	A minimum of four decision-makers will be identified: the CEO, CNO, clinical head of pediatric surgery and clinical head of pediatric medicine. Hospitals with more than 80 beds will identify 2 additional decision-makers; hospitals with more than 120 beds will identify 4 additional decision-makers, and hospitals with more than 180 beds will identify an additional 6 decision-makers

**Table 4 Tab4:** **Clinical deterioration events**

		**Definition**	**SCDE***
1	Early transfer	<60 ml/kg intravenous or intraosseous fluid resuscitation given in the 12 h before transfer, no intravenous or intraosseous inotrope or vasoactive medications and no positive pressure ventilation (bag mask or endotracheal) in the 12 h before transfer	No
2	Noninvasive respiratory support	Positive pressure ventilation in the 12 h before transfer, but not intubated at the time of transfer. This category includes children receiving mask-delivered positive airway pressure at any stage in the 12 h before transfer and at the time of transfer. Mechanical ventilation during anesthesia for a scheduled procedure is not included	No
3	Invasive respiratory support	Intubated and/or receiving endotracheal ventilation at the time of transfer or intubated within 1 h of PICU admission	Yes
4	Circulatory	>60 ml/kg intravenous or intraosseous fluid resuscitation given in the 12 h before transfer, and administration of any intravenous or intraosseous inotrope or vasopressor at the time of transfer or at any stage in the 12 h preceding transfer. Patients in this category may also receive positive pressure ventilation (2)	Yes
5	Late transfer	Respiratory (3) *and* circulatory (4) support before transfer	Yes
6	Cardiopulmonary resuscitation	Chest compressions before transfer from ward area or within 1 h of PICU admission or ECMO instituted before or within 1 h of PICU admission	Yes
7	Death	Death on an inpatient ward, other than in those patients with DNR orders. Death may occur despite CPR (or intention to perform CPR if patient is pronounced dead without CPR). No transfer from ward area	Yes

*ECMO* extracorporeal membrane oxygenation therapy.

**SCDE* significant clinical deterioration event.

**Table 5 Tab5:** **Potential preventability criteria**

**Rating**	**Category**
1	Virtually no evidence of preventability
2	Slight-to-modest evidence of preventability
3	Preventability not quite likely (less than 50/50, but “close call”)
4	Preventability more than likely (more than 50/50, but “close call”)
5	Strong evidence of preventability
6	Virtually certain evidence of preventability

Criteria used to determine potential preventability in EPOCH. These criteria were used in the Canadian Adverse Events Study. A rating of 4 or more will be regarded as a high degree of preventability. Potentially preventable cardiac arrests will be presented as rate per thousand patient-days.

### Secondary outcomes: process of care

The study includes five processes of care assessments: (1) ‘Stat’ calls. This was formally defined (Table 3), and a consistent approach to data collection was applied throughout the study, recognizing that cultural and other factors may contribute to considerable inter-hospital variability. (2) Code Blue calls for immediate medical assistance of the resuscitation team and equipment. (3) Urgent consultations (within 15 min) to the ICU or MET-RRT. (4) Using documentation from five randomly (central computerized randomization) selected patients each week, physician visits, the nurse:patient ratio and the use of continuous monitoring are described. (5) Frontline staff complete the documentation and interaction survey (2 pages, <10 min to complete) that describes their perceptions of the documentation system and the nature of interactions with physicians (Additional file 2: CRF). This custom-built survey was developed and used in our pilot evaluations of BedsidePEWS. It has not been formally validated.

### Secondary outcomes: resource utilization and decision-maker perceptions

Resource utilization is assessed in all hospitals by measurement of hospital length of stay and for patients undergoing urgent ICU admission, ICU length of stay and the days of use of the ICU technologies: mechanical ventilation, hemodialysis, ECMO and nitric oxide. A purpose-built survey of the perceptions of hospital decision-makers will be conducted 3 months after the end of the 12-month intervention period (Table 3) to describe the experience of the decision-maker in participating in a hospital-wide cluster RCT and their expectations of its results.

All outcomes are assessed prospectively. The first 26 weeks are baseline data. Then following a 5-week run-in period in intervention hospitals or break from data collection in control hospitals, outcomes are assessed prospectively for 52 weeks (Additional file 1).

### Sample size and assumptions

Power calculations are based on population estimates derived from 14 local hospitals’ data using a published method for cluster RCTs [61]. For all-cause mortality we found a baseline rate of 5.1/1000. The steering committee agreed that a mortality reduction of less than 1/1000 admissions would not be a compelling reason to modify practice. A study with 20 hospitals can show an 18% relative risk reduction in mortality (absolute risk reduction 0.09%), given alpha = 0.05 (2-sided), power = 80%, mean of 119 pediatric beds, length of stay = 4 days, with 0.90 average occupancy, k = 0.15, *n* = 20, baseline rate = 5.1/1000. The quantity k is the coefficient of variation for mortality between hospitals. Assuming attrition of 1-2 hospitals, we will include a sample of 22 hospitals.

Data from 4 pediatric hospitals in Ontario indicate there are 1052 urgent ICU admissions/year, of which we estimate 40% involve SCDE, for a rate of 2 per thousand patient days. Thus, with 20 sites we will be able to show a 31% reduction in SCDE [alpha = 0.05 (2-sided), power = 80%, k = 0.15, where k is the coefficient of variation for SCDE rate between hospitals]. The value of k allows for a moderate amount of clustering within hospital.

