## Discussion

Preliminary data suggest that the BedsidePEWS score can identify patients at risk for near and actual cardiopulmonary arrest, can be calculated both rapidly and reliably and that its clinical implementation is associated with potential improvements in patient and process of care outcomes. The resource implications of system-wide implementation, the previous lessons from the MERIT study, and the uncertain effect on important clinical outcomes underscore the relevance of the cluster-randomized design, the selection of the intervention and the outcomes used in EPOCH. EPOCH will be conducted in 22 hospitals, involve an estimated 100,000 patients admitted for about 400,000 patient-days and describe approximately 1900 urgent ICU admissions, 200 cardiac arrest events and 500 deaths. Mortality in hospitalized children is an objective measure of quality of care and is used extensively to benchmark the performance of PICUs [58,63-66], surgical programs and hospitals [67-69].

All-cause hospital mortality was selected as the primary outcome in EPOCH for the following reasons. First, mortality is objective and can be reliably assessed. Second, a reduction in all-cause hospital mortality is the ultimate goal of any intervention to improve the outcomes of care of hospitalized children. Third, observational studies of MET-RRT have reported reduced all-cause mortality [36,38]. Fourth, several studies show that when children who have been hospitalized die, most do so in hospital [70-73]. In a 6-year study of in-ICU cardiac arrest, we found only one (1.4%) additional death after index-hospitalization discharge and within 12 months of the index cardiac arrest. Fifth, the effect of pediatric palliative care services on displacing place of death to home or hospice is small [72,74-77]. One large US study found the proportion of deaths in the hospital decreased by less than 6% (from 85.7 to 80.1%) over a 10-year period [75]. Thus, measuring hospital mortality provides a reasonably accurate measure of mortality in children who have been or are currently hospitalized.

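### With the stated inputs, 20 hospitals give about 51-55% unadjusted power for an 18% mortality reduction; the effect detectable with 80% power is about 24-25%

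*Protocol article*

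**What the plan says.** All of the power inputs are in the protocol article, Methods, under Sample size and assumptions.

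- **Claim for the primary outcome:** "A study with 20 hospitals can show an 18% relative risk reduction in mortality (absolute risk reduction 0.09" per cent), "given alpha = 0.05 (2-sided), power = 80" per cent.
- **Baseline rate:** "For all-cause mortality we found a baseline rate of 5.1/1000".
- **Hospital size and clustering:** "mean of 119 pediatric beds, length of stay = 4 days, with 0.90 average occupancy, k = 0.15". The section defines k as the coefficient of variation of mortality between hospitals.
- **Number of hospitals:** 20 is the trial total, because 22 are enrolled only to cover the loss of one or two. Randomization is 1:1, so there are 10 hospitals per arm.
- **Threshold for changing practice:** the steering committee agreed that "a mortality reduction of less than 1/1000 admissions would not be a compelling reason to modify practice".
- **Method:** a published method for cluster trials is cited, but the article does not name it or give its formula.
- **Main secondary outcome, significant clinical deterioration events (SCDE):** "Thus, with 20 sites we will be able to show a 31% reduction in SCDE", at the same alpha, power and k. No cluster size is given in that sentence.

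The outcome period is 52 weeks after a 26-week baseline (end of the section on resource utilization outcomes). The primary analysis adjusts for the baseline mortality logit and the size stratum. The Discussion expects the 22 hospitals to "involve an estimated 100,000 patients admitted for about 400,000 patient-days and describe approximately 1900 urgent ICU admissions, 200 cardiac arrest events and 500 deaths".

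**The concern.** The 18% corresponds to 0.92 deaths per 1000, just below the committee's 1 per 1000. As written, the trial appears to have 80% power for the smallest effect the committee considered worth acting on. With only 10 hospitals per arm, between-hospital variation at k = 0.15 takes up much of the available precision, and 18% looks too small to be detectable.

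The interpretation of a null result is at stake. The abstract and the Discussion say that a negative trial would let hospitals avoid the cost of implementation. That inference needs good power at 1 per 1000. If the trial lacks it, a non-significant mortality result would be compatible with a benefit the committee itself regards as worth having.

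**Working it through.** **Inputs.** p0 = 0.0051, alpha = 0.05 two-sided, power 80%, k = 0.15, 10 hospitals per arm. Admissions per hospital-year: m = 119 x 0.90 x 365 / 4 = 9,773.

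**The plan's own figure.** 5.1 x 0.18 = 0.918 per 1000, or 0.09%, so the relative and absolute reductions agree with each other. The intervention rate is p1 = 0.004182.

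**Formula (assumed, since the cited method is not shown).** The usual coefficient-of-variation formula for unmatched clusters gives the number per arm as

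c = 1 + (1.96 + 0.8416)^2 x [ (p0(1-p0) + p1(1-p1))/m + k^2(p0^2 + p1^2) ] / (p0 - p1)^2

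- Within-hospital term: 9.453e-7
- Between-hospital term: 9.787e-7
- Squared difference: 8.427e-7
- c = 1 + 7.849 x 1.924e-6 / 8.427e-7 = 18.9 per arm

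With a correction of 0 or 2 clusters in place of 1, c is 17.9 or 19.9. So 18% needs about 18-20 hospitals per arm.

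**Power at 18% with 10 per arm.** With the +1, SE = sqrt(1.924e-6 / 9) = 4.62e-4, so 0.000918 / SE - 1.96 = 0.03 and power is 51%. Without it, SE = sqrt(1.924e-6 / 10) = 4.39e-4 and power is 55%.

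**Solving for the detectable effect**

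| Hospitals per arm | Power at 18% | Power at 1 per 1000 | Effect at 80% power |
|---|---|---|---|
| 10 | 51% (+1), 55% (no correction) | 59%, 63% | 24.8%, 23.6% (1.26, 1.20 per 1000) |
| 11 | 55%, 59% | 63%, 67% | 23.6%, 22.6% (1.20, 1.15 per 1000) |

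**Other variants that keep 20 hospitals, k = 0.15 and the stated volumes.** A t reference on 18 df gives 50.8% power at 18%, a design-effect calculation 53.5%, a one-sided test 63-67%, and pooling 78 weeks of data 58-63%. None reaches 80%.

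**What returns about 18%.** Each of these changes a stated or implied input:

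- 20 hospitals per arm: 17.5% with the +1, 18.0% with +2
- k = 0: 17.8% with the +1
- k = 0.05 without the +1: 17.8%
- no within-hospital sampling error: 18.1% with the +1

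**Credit for baseline adjustment.** If hospital effects are stable and the baseline is half as long, the correlation between the two periods is 5.85 / sqrt((5.19 + 5.85)(10.38 + 5.85)) = 0.44, where 5.19 and 5.85 are the within- and between-hospital variances in units of 1e-7. Residual variance falls to 1 - 0.44^2 = 0.81 of its value, and power at 18% is 60-64%. If adjustment instead removed 75% of the between-hospital variance, power would be 71% with the +1 and 76% without it.

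**Volumes (a separate check).** The inputs imply 22 x 9,773 = 215,000 admissions, 860,000 patient-days and 1,100 deaths in one year. The Discussion gives 100,000, 400,000 and 500. Length of stay (4 days) and mortality (5 per 1000) agree, so only the volume differs. With the +1 and 10 per arm:

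- 100,000 / 22 = 4,545 per hospital: detectable effect 30%, power at 18% is 35%.
- 4,545 x 52/78 = 3,030, if the 100,000 includes the baseline period: 35% and 28%.

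**SCDE.** Using the same formula for a rate of 2 per 1000 patient-days, with the +1 and 10 per arm:

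- 31% corresponds to about 11,000 patient-days per hospital-year.
- The Discussion's volume spread over 78 weeks gives 400,000 / 22 x 52/78 = 12,121 patient-days and a detectable effect of 30.1%.
- The 119-bed inputs give 39,092 patient-days and 22.6%.

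**The case against.** The strongest defence is that the formula is an assumption. The cited method is not visible, and the article does not say whether k is before or after stratification. This stands as a caveat. It does not rescue the figure, because no variant tried that keeps 20 hospitals, k = 0.15 and the stated volumes reaches 80%.

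The second is that the primary model adjusts for baseline mortality, so 51-55% is not the power of the planned analysis. That is right, and the figure must be labelled unadjusted. A reader might infer that the trial's real power is 51%; the documents do not support that. But the sample-size section credits no adjustment, and the scenarios above leave power below 80%.

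Three further inferences are tempting and go too far:

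- **That n = 20 was entered per arm.** It fits the numbers, but so do several other changes of input. The documents do not show the cause.
- **That the 31% for SCDE is wrong because SCDE events would outnumber deaths.** That imposes the 119-bed volume on a sentence that states no cluster size. At 11,000-12,000 patient-days per hospital-year, 31% is about right; at larger volumes it is conservative.
- **That the Discussion's lower volume confirms the error in the 18%.** It is a separate inconsistency and has no bearing on whether 18% follows from the sample-size inputs.

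The limitations section does concede that deaths may be too infrequent to show important differences. That softens the consequence but does not correct the stated figure.

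**Conclusion.** The stated detectable mortality reduction does not follow from its stated inputs. Under the usual unmatched formula without baseline adjustment, 10 hospitals per arm give about 51-55% power at 18% and 59-63% at 1 per 1000. The 80%-power effect is about 24-25% (22.6-23.6% with all 22 hospitals retained). The 18% would take roughly twice as many hospitals.

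The arithmetic is firm given the formula. The size of the shortfall in the planned analysis is less certain: with baseline adjustment, power at 18% is plausibly about 60-71%, depending on how stable hospital mortality is between periods.

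The volume mismatch with the Discussion is real and would lower power further if the smaller figure is the realistic one. Whether the 100,000 covers 52 or 78 weeks is not stated, so 30% and 35% are scenarios.

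**What to change.** 1. Under Sample size and assumptions, replace the 18% with the effect detectable at k = 0.15: about 24-25% for 10 hospitals per arm and 22.6-23.6% for 11. Equivalently, give about 51-55% power at 18% and 59-63% at 1 per 1000 for 10 per arm. Label these as unadjusted and give the formula used.
2. If baseline adjustment is to be credited, state the assumed correlation between periods and the resulting power.
3. Separately, use one set of volumes in the sample-size section and the Discussion, and say which weeks the 100,000 patients cover. If that figure is the realistic one, quote about 30%, or 35% if it includes the baseline period.
4. State the cluster size behind the 31% for SCDE. The figure itself need not change unless that size shows otherwise.
5. In the abstract and Discussion, say that a non-significant mortality result will be read from its confidence interval against 1 per 1000, and will not by itself show that implementation costs can be avoided.

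The cost is text only. No hospitals are added and the analysis is unchanged, which matters because enrolment was already complete according to the Trial status section. The stated power becomes less favourable.

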### Data analysis

Demographic and unadjusted outcomes data will be reported using means, median, variances, interquartile ranges or as proportions with 95% confidence intervals. Outcomes will be reported for the baseline and intervention periods for each hospital consistent with published recommendations for cluster randomized trials [62].

#### Primary analysis

All-cause hospital mortality will be evaluated using a logit regression model. The dependent variable will be the logit of the proportion dying in each hospital. The independent variables will include a dummy indicator for treatment arm, the baseline mortality logit and the hospital size stratification variable. The analysis will be weighted by the size of the hospital.

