## Methods

EPOCH is a cluster-randomized trial comparing the BedsidePEWS with standard care (no severity of illness score) in hospitals with a pediatric intensive care unit (ICU). The unit of randomization is the participating hospital. Eligible hospitals provide care for more than a total of 200 eligible inpatient admissions in eligible inpatient wards each year, have specialized pediatric physicians and have at least one PICU. Eligible inpatient wards are defined as areas where care is provided to children who are admitted to the hospital, other than the NICU, PICU, operating rooms and other designated areas where anesthetist-supervised procedures are performed. Emergency departments that care for admitted patients may be regarded as an eligible ‘ward’ (Table 2). Eligible patients are >37 weeks gestational age and <18 years, and they have received care in an eligible inpatient ward. To ensure that major system changes do not introduce bias, we will exclude hospitals that plan to introduce or discontinue an MET-RRT during the study, are already using a severity of illness score in wards or consider randomization unacceptable. Hospitals with a pre-existing MET-RRT are eligible to participate.

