#### Secondary analyses

An identical logit model will be used for ICU mortality after urgent ICU admission where the PICU admission was initiated in a hospital ward, ICU mortality after urgent ICU admission initiated in the OR, unplanned hospital re-admission within 2 days of hospital discharge and mortality following DNR orders.

Significant clinical deterioration events, Code Blue events, stat calls and urgent PICU consultations per 1000 patient-days will be evaluated using Poisson regression using hospital-level aggregated count data. The independent variables will include a dummy indicator for treatment arm, the baseline event rate and hospital size stratification variable. A linear regression model, in which the within-hospital mean is the dependent variable, will be used to evaluate the nature of SCDE, inpatient ward patient-days, and for patients admitted urgently to the PICU, PIM2 score, PELOD score, ventilator-free days, ICU patient-days and ICU therapy-days. The independent variables will include a dummy indicator for treatment arm, the baseline means and hospital size stratification variable. The analysis will be weighted by the size of the hospital.

An identical linear regression model will be used to evaluate the frequency of vital sign documentation from the randomly selected patient records. Since the number of records abstracted will be the same in each hospital, weighting will not be necessary. Documentation will be evaluated as follows: the number of heart rate, respiratory rate, systolic blood pressure, trans-cutaneous oxygen saturation, capillary refill, oxygen therapy and respiratory effort measurements, and the number of times that all seven items were documented will be compared for patients in hospitals with and without BedsidePEWS. All analyses will adjust for baseline event rates and hospital strata. Linear regression will be used to compare the numbers of (1) vital signs documented, (2) documented physician visits, (3) the nurse: patient ratio, the use of (4) continuous ECG monitoring and (5) continuous pulse oximeter monitoring with the BedsidePEWS scores calculated from the abstracted clinical data.

Analysis of the documentation and interaction survey and the post-study decision-maker survey data will compare groups using linear regression weighted by the size of the hospital.

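### The hospital-level logit models have no value for a hospital with zero events, and size-only weights do not fit the assumed between-hospital variation

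*Protocol article*

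**What the plan says.** The Primary analysis section describes a regression with one value per hospital: "The dependent variable will be the logit of the proportion dying in each hospital". The covariates are "a dummy indicator for treatment arm, the baseline mortality logit and the hospital size stratification variable". It adds: "The analysis will be weighted by the size of the hospital".

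The Secondary analyses section carries the model over: "An identical logit model will be used for ICU mortality after urgent ICU admission". The list covers ward-initiated and OR-initiated urgent admissions separately, and also unplanned re-admission and mortality after DNR orders.

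Three other statements bear on how often a hospital will have no events:

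- Methods sets a low entry threshold: "Eligible hospitals provide care for more than a total of 200 eligible inpatient admissions in eligible inpatient wards each year".
- The section on resource utilization outcomes sets a 26-week baseline and a 52-week outcome period.
- Sample size and assumptions states: "For all-cause mortality we found a baseline rate of 5.1/1000". It also gives the mean hospital ("given alpha = 0.05 (2-sided), power = 80%, mean of 119 pediatric beds") and "length of stay = 4 days, with 0.90 average occupancy, k = 0.15", where k is the between-hospital coefficient of variation of mortality.

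The article gives no rule for a hospital with zero events.

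**The concern.** The logit of zero is minus infinity. A hospital with no deaths in the 52-week period has no outcome value, and one with no deaths in the 26-week baseline has no covariate value. Either way a randomized hospital leaves the analysis, or someone chooses a correction after seeing the data. The design allows for losing only one or two hospitals. The ICU-mortality outcomes are much sparser than hospital mortality, so there the problem is the normal case.

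The weights raise a second, smaller issue. Weighting by size is right when a hospital logit's variance is proportional to 1/size. The sample size section instead assumes real variation between hospitals, which adds a component that does not shrink with size. Size weights then lean too heavily on the largest hospitals, and the model-based standard error can be too small.

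**Working it through.** **Inputs from the article.** Mortality 5.1/1000, 119 beds, 0.90 occupancy, 4-day stay, k = 0.15, 22 hospitals, periods of 26 and 52 weeks. The Discussion gives 100,000 patients, about 500 deaths and about 1,900 urgent ICU admissions.

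**Assumed, because the article does not give them.** Hospital-size coefficient of variation (CV) 0 to 1.0, baseline-to-outcome correlation of hospital effects 0.5 to 1, and ICU mortality 3-10%.

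**Two volumes.** Sample size section: 119 × 0.90 × 365/4 = 9,773 admissions per hospital-year, or 9,773 × 0.0051 = 49.8 deaths a year and 24.9 in the baseline. Discussion: 100,000 × 0.0051 = 510, which agrees with its roughly 500 deaths. Spread over 22 hospitals and 78 weeks (my reading), that is 100,000/22 × 52/78 = 3,030 per hospital-year, or 15.5 deaths a year and 7.7 in the baseline. The two volumes differ about threefold, so I carry both.

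**Zero deaths in one hospital**, P(0) = (1 − 0.0051)^n:

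| Admissions/year | P(0), 26 weeks | P(0), 52 weeks |
|---|---|---|
| 200 | 60% | 36% |
| 500 | 28% | 7.8% |
| 1,000 | 7.8% | 0.6% |
| 9,773 | about 1e-11 | negligible |

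**At least one undefined hospital among 22, and type I error.** I simulated under no effect (4,000 trials per row, k = 0.15), adding 0.5 to counts so that every logit exists. Sizes follow a fixed spread with the stated CV. Monte Carlo standard error near 5% is √(0.05 × 0.95/4000) = 0.3 points.

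| Size CV | Baseline correlation | 9,773/yr: any zero | size-weighted | unweighted | 3,030/yr: any zero | size-weighted | unweighted |
|---|---|---|---|---|---|---|---|
| 0.8 | 0.5 | 0.9% | 8.0% | 4.9% | 50% | 6.3% | 4.7% |
| 0.8 | 1 | 1.1% | 6.5% | 5.1% | 49% | 6.0% | 4.8% |
| 1.0 | 0.5 | 4.9% | 9.0% | 4.8% | 72% | 5.8% | 4.0% |
| 1.0 | 1 | 4.5% | 7.1% | 5.1% | 73% | 6.3% | 4.3% |

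With sizes drawn afresh in each trial and CV 0.6-1.0, the chance of any zero is about 0.3-9% at the first volume and 29-72% at the second. Most zeros fall in the 26-week baseline. At the first volume, size-weighted type I error is 4.4-5.6% with equal sizes, 5.0-5.8% at CV 0.4 and 5.7-7.2% at CV 0.6. The unweighted version stays at 4.0-5.6% throughout.

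**Why the weights matter.** The variance of a hospital logit is roughly 1/deaths + k². At 9,773 admissions this is 1/49.8 + 0.15² = 0.020 + 0.0225, so the part that size weights leave out is as large as the part they keep. At 3,030 it is 1/15.5 + 0.0225 = 0.065 + 0.0225. Sampling error dominates there, and the inflation is smaller.

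**ICU mortality.** 1,900/22 = 86.4 urgent admissions per hospital, taken as one third in the baseline and two thirds in the outcome period, with equal sizes and both ICU outcomes pooled. For mortality q, the expected deaths are 28.8q and 57.6q. P(undefined) = 1 − (1 − e^(−28.8q))(1 − e^(−57.6q)).

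- q = 10%: 1 − (1 − 0.056)(1 − 0.003) = 0.059; × 22 = 1.3 hospitals.
- q = 5%: 1 − (1 − 0.237)(1 − 0.056) = 0.280; × 22 = 6.2 hospitals.
- q = 3%: 1 − (1 − 0.422)(1 − 0.178) = 0.524; × 22 = 11.5 hospitals.

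Reporting ward-initiated and OR-initiated admissions separately, as planned, makes zeros more frequent.

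**The case against.** The threshold of 200 admissions is a floor, not an expected size. At a 4-day stay and 0.90 occupancy it means 200 × 4/(0.90 × 365) = 2.4 beds, which is hard to picture in a hospital with a PICU. This stands: at the planned mean size the zero-death problem is remote for the primary outcome. It does not answer the Discussion's total, where the average hospital has fewer than eight baseline deaths, or the ICU outcomes.

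A reader might infer that the analysis selectively drops the hospitals with the lowest mortality. The article does not say that such hospitals are dropped. Most zeros would fall before implementation, and they would come mainly from small size. A hospital at the floor would carry only 200/(22 × 9,773) = 0.09% of the size weight. The supportable point is that the model cannot be computed as written, not that it is biased in a known direction.

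A reader might also infer that the test ignores between-hospital variation, or that its type I error exceeds 5% outright. Neither follows. A regression on hospital values estimates its residual variance from scatter between hospitals, and with equal sizes the error is nominal. A grouped binomial model with no between-hospital term would give 14-24% at k = 0.15 and the planned volume, but the stated dependent variable argues against that reading.

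Finally, a zero-count correction is often left to an analysis plan, and one may exist. But the article fixes the outcome, the covariate and the weights, and any zero forces a change to that stated model.

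**Conclusion.** The point holds in a limited form. The logit models as written are undefined for any hospital with zero events in either period. For the primary outcome this is unlikely at the sample size section's volume (about 0.3-9%) and realistic at the Discussion's (about 29-72%), both with an assumed size CV of 0.6-1.0. For ICU mortality it is to be expected: about 1 to 12 of 22 hospitals at an assumed 10% to 3% mortality. I did not assess re-admission or mortality after DNR orders, so nothing here shows that those models would fail.

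The weighting issue is real but modest. Type I error is nominal with equal sizes. With widely differing sizes it is about 6-9% at the planned volume and about 6-7% at the 100,000-patient volume. The article does not give the spread of hospital sizes, so the actual inflation is unknown. The worst figures should not be combined: the larger inflation belongs to the volume at which zeros are rare.

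**What to change.** Before analysis, choose one of two forms and apply it also to the secondary logit models.

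1. A binomial model for deaths out of admissions per hospital, with overdispersion or a hospital random effect. Include arm, size stratum and a baseline logit computed with 0.5 added to the counts. Test against a t distribution on hospital degrees of freedom: 22 hospitals less 4 coefficients gives 18 if all hospitals stay.
2. The two-stage regression, with 0.5-corrected logits for both outcome and baseline. Use either no weights or weights 1/(1/expected deaths + τ²), where τ² is the between-hospital variance on the logit scale. Expected deaths must come from the hospital's admissions and the overall rate. Observed deaths would give a zero-death hospital no weight and tie the weights to the outcome.

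The second form is the smaller change, and the unweighted version held its error rate in every scenario above. The cost is analysis wording and code; no data collection changes.
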